## Abstract

**Introduction:**

Photobiomodulation (PBM) is a novel strategy for cognitive enhancement by improving brain metabolism and blood flow. It is potentially beneficial for patients with Alzheimer’s disease (AD). We present a study protocol for a randomised controlled trial designed to evaluate the efficacy and safety of PBM.

**Method and analysis:**

This is a single-centre, parallel-group, randomised, sham-controlled study. We enroll patients with mild cognitive impairment or dementia due to AD and assigned them to receive either active or sham stimulation at home for 12 weeks, with three sessions per week (20 min each). The stimulation involves invisible near-infrared light delivered by five applicators (one in a nostril, one on the frontal scalp, and three on the occipital scalp). The primary outcome will be the mean change in the Alzheimer Disease Assessment Scale-cognition from baseline to Week 12. We will also measure cognitive function, activity of daily living, behavioral and psychological symptoms, and caregiver burden. We will collect data at clinics at baseline and Week 12 and remotely at home. We estimate a sample size of 30 (20 active and 10 sham) based on an expected mean difference of −6.9 and an SD of 4.8. We use linear models for the statistical analysis.

**Ethics and dissemination:**

The National Center of Neurology and Psychiatry Clinical Research Review Board (CRB3200004) approved this study. The results of this study will be published in a scientific peer-reviewed journal. Trial registration details Japan Registry of Clinical Trials jRCTs032230339.

## Introduction

Dementia is a clinical syndrome characterized by impaired cognitive functions and reduced capacity to perform daily activities, as well as affecting the quality of life and social well-being of their caregivers. Prior to dementia, there is a stage of mild cognitive impairment, which is a condition of decreased cognitive performance that does not meet the criteria for dementia and preserves their ability for independent living (1). While some pharmacological treatments are available, such as cholinesterase inhibitors, memantine, and anti-amyloid antibodies, their efficacy and safety are still under debate. Anti-amyloid antibodies, in particular, have been recently approved in the United States and Japan, but their high cost, modest benefit, and potential risk of causing amyloid-related imaging abnormality, which can be fatal, raise questions about their clinical utility (2). Besides pharmacological interventions, several modifiable factors, such as physical activity, social engagement, and depression, have been identified as possible risk or protective factors for dementia (3).

Photobiomodulation (PBM) is a light therapy method that employs visible light (wavelengths around 400–700 nm) and near-infrared light (wavelengths around 810–1,100 nm). Its potential was first unveiled in 1968 when Mester et al. reported the positive effects of PBM on hair growth and wound healing in mice using a ruby laser (4). Since then, PBM has been investigated under various terms, including low-reactive level laser therapy (LLLT). More recently, it has been shown that light-emitting diodes (LEDs), which are more cost-effective than lasers, can also produce comparable results. Consequently, PBM encompasses interventions that utilize various types of light sources beyond lasers.

The mechanism underlying PBM’s effects varies depending on the wavelength of the light used. Notably, light in the red-near-infrared region offers superior tissue penetration and contributes to cell proliferation and growth promotion (5, 6), conversely, blue region light is expected to exhibit effects such as bactericidal effect and induction of cell apoptosis at high irradiation levels. In the case of low-level irradiation of red-near-infrared region light, it is believed that photons are absorbed by intracellular chromophores present in intracellular organelles (especially within mitochondria). Cytochrome C oxidase (CCO) is involved as a light receptor for this process (7), and the activation of CCO increases ATP production and activates cellular metabolic activity. It is also thought that the reactive oxygen species (ROS) and nitrogen oxide (NO) generated in this process promote gene transcription and cell repair. NO also has a role in regulating neurotransmitters in the central nervous system and vasodilation, which is thought to improve blood circulation. As a result, increased cerebral blood flow (8) and increased brain metabolism (9) have been observed with transcranial PBM.

The field of PBM has witnessed significant progress in improving brain stimulation parameters. Notably, the shift from continuous to pulsed stimulation has shown potential benefits, enhancing tissue absorption responses and possibly inducing specific brain wave rhythms, such as alpha waves at 10 Hz and gamma waves at 40 Hz (10). Furthermore, intranasal PBM may be related to direct or indirect stimulation of deeper brain regions (11), such as ventromedial prefrontal cortex and ventromedial orbitofrontal cortex (12). Coupled with the cost-effectiveness and miniaturization of LED devices, these improved parameters have heightened expectations for the effectiveness of PBM in neurological and psychiatric applications, especially in the context of cognitive enhancement. Consequently, a surge of clinical studies is expected to assess its impact in these domains. While the effectiveness of 40 Hz PBM on amyloid load in mice has yielded mixed results (13, 14), several clinical trials have shown potential in enhancing cognitive function in dementia patients.

For example, a sham-controlled clinical study by Chan et al. involved treating 18 patients with nine LEDs during a single stimulation session, which resulted in improved visual memory (15). Saltmarche et al. employed 5 patients, using pulsed 810 nm light at 10 Hz with an intensity of 14.2 mW/cm^2^ for sessions lasting 25 min, conducted once or twice weekly over 12 weeks, and observed improvements in Mini-Mental State Examination (MMSE (16)) and Alzheimer’s Disease Assessment Scale-Cognitive subscale (ADAS-Cog (17)) scores compared to baseline (18). Similarly, (19) Berman et al. recruited 11 patients and adopted pulsed 1,072 nm light at 10 Hz for 6 min daily over 28 consecutive days, noting improvements in quantitative electroencephalogram compared to a sham stimulation group (20). Nizamutdinov et al. administered continuous 1,060–1,080 nm light at an intensity of 23.1 mW/cm^2^ for sessions lasting 6 min, twice daily over 12 weeks to 60 patients, and reported improvements in MMSE and LMT-I scores compared to a sham stimulation group (21).

While the above paper used transcranial PBM, another clinical study has also used a nasal applicator to stimulate the deep brain trans nasally. Chao et al. utilized pulsed 810 nm light at 40 Hz with an intensity of 75 mW/cm^2^ for 20 min sessions thrice weekly over 12 weeks to 8 patients, reporting enhancements in ADAS-Cog and NPI scores compared to a sham stimulation group (19). This article also suggests increased cerebral perfusion and connectivity between the posterior cingulate cortex and lateral parietal nodes within the default-mode network in the PBM group. Our study try to extend this evidence with more number of participants in Japan to evaluate the utility of transcranial and intranasal PBM in early Alzheimer’s disease (AD) patients, who are expected to exhibit mild neurodegeneration due to dementia.

## Methods and analysis

### Objective

The main objective of this study is to assess the effectiveness and safety of 12 week photobiomodulation on cognition among mild cognitive impairment and mild dementia due to AD patients as assessed by ADAS-Cog.

### Trial design

This is a prospective, parallel, randomised, sham-controlled, superiority trial involving 30 participants with AD-related mild cognitive impairment or dementia, as per the DSM-5 criteria. The participants will be allocated to either an active or a sham group in a 2:1 ratio. The protocol adheres to the 2013 SPIRIT guidelines (22). The trial is registered with the Japan Registry of Clinical Trials (Trial ID: jRCTs032230339).

### Participants

We will enroll outpatients with regular consultations from a single academic hospital in Tokyo, Japan: the National Center of Neurology and Psychiatry. Potential participants will be referred by their treating psychiatrists or neurologists and receive a brochure with brief information on the trial after their initial appointments. Participants who express interest will provide informed consent to the principal investigator or subinvestigators using the Informed Consent Form (Supplementary File S1). The study design, benefits and risks will be explained to the participants by the principal investigator and outcome assessors. Participants will undergo screening by a treating psychiatrist to verify their eligibility (shown below). The inclusion criteria are: (1) Age between 60 and 90 years at consent, (2) Prior visit to the study site, (3) Early AD diagnosis (mild AD or MCI due to AD) confirmed by the Diagnostic and Statistical Manual of Mental Disorders, Fifth Edition, Text Revision (DSM-5-TR) at the study site, (4) MMSE score between 15 and 30 points, (5) Availability of a study partner who cohabits or regularly (defined by 10 h or more per week) monitors the participant’s condition, (6) Ability to communicate and complete questionnaires via the internet or email, using a smartphone or personal computer (with or without study partner assistance), (7) Stable treatment for early AD (no change in drug or non-drug therapies for more than 4 weeks), (8) no major environmental changes expected within 12 weeks after the trial initiation, such as hospitalization, travel, relocation. The exclusion criteria are as follows; (1) people with cognitive impairment from causes other than AD (such as mental disorders, intellectual disabilities, etc.), (2) people who join a new clinical trial or study during this study period, (3) people with skin problems or foreign materials that interferes appropriate photobiomodulation, (4) people who are not suitable for this study according to the principal investigator or subinvestigators.

### Intervention

The study will employ a home-based PBM intervention using the Vielight Neuro Gamma 4 device (Vielight Inc., Tronto, Ontario, Canada), which delivers near-infrared emissions via five LED applicators (one intranasal, one frontal, and three occipital). The device will target the frontal, temporal, occipitoparietal, and naso-temporal regions (see Figure 1). Subjects will blindly receive either active or sham devices from the investigator at the time of study entry. At that time, the investigator will adjust the device to the appropriate angle and instruct the subject and study partner on the appropriate way of its use. The subject and study partner will be responsible for the daily removal and recharging of the device, and they will have free access to the device instructions and instructional videos created for the study. They will also report and communicate regularly with researchers to check for malfunctions and failure of the device.

The participants will be randomised into two groups: active or sham PBM. The active group will receive 40 Hz intermittent photoemission per session with 60 J/cm^2^ on the frontal region, 45 J/cm^2^ on the occipital region in total, and 15 J/cm^2^ intranasally. The sham group will receive a placebo device that mimics the appearance of the active device but does not emit any light for 20 min per session.

Regarding the dosage, it is thought that effective effects on cells emerge when a heat value of 0.1–6 J/cm^2^ is transferred as the effect of PBM on the skin surface,^1^ and considering the energy loss in the pathway, this product is designed to deliver 60 J/cm^2^ in the frontal region, 45 J/cm^2^ in the occipital region, and 15 J/cm^2^ in the nasal cavity in order to stimulate cranial nerves at a deeper level. Based on the output power of the product (100, 75, and 25 mW/cm^2^, respectively), the irradiation time is calculated to be 20 min (1,200 s).

Both devices will have a green light indicator and will turn off automatically after 20 min. The participants and their study partners are taught to do PBM at their home or wherever comfortable three times a week within the same range of a day (morning, afternoon, or evening). They will be unable to discern whether they are using the active or sham device. The assessors and participants will be blinded to the treatment allocation to enhance the study validity. At the end of Week 12, the participants will be asked to guess their treatment group to assess the blinding quality. The participants and their study partners will also monitor and report any adverse events to the researchers remotely, as well as submit periodic reports of efficacy, safety, and satisfaction. The study partners will keep track of the device usage frequency and occasionally contact the participants or their partners to encourage adherence to the study protocol.

Any changes in the concomitant therapy of the participants, such as starting, stopping, or adjusting the dose, should be documented, and reported to the researcher. The researcher will train the patient and study partner on operating the device at home and provide written instructions before the first use. The researcher will also verify that the patient and study partner can use the device correctly. A video tutorial is available for reference at any time, and any issues or questions regarding the device use are regularly monitored to enhance adherence. The participant will be withdrawn from the study if any of the following conditions apply, as determined by the principal investigator or subinvestigators when the participant revokes their consent or asks to stop participating in the research; the participant is affected by a disease outbreak or a pandemic; the device shows insufficient efficacy for the participant; the participant fails to attend the evaluation and cannot be reached; the principal investigator or subinvestigators judge that the participant’s mental and physical burden is too high to continue in this study; there is a serious breach or violation of the research protocol. The entire study may be terminated by the Independent Safety and Effectiveness Committee, which convenes when three or more serious adverse events related to the study device occur.

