## Outcomes

The main outcome of interest is mean change in ADAS-Cog scores from baseline to Week 12 between groups. ADAS-Cog is the *de facto* standard scale developed for assessing anti-dementia treatment. Other outcomes include global function, assessed by Clinical Dementia Rating scale; quality of life, evaluated by the DEMQOL (23) and DEMQOL-proxy (24); cognition, measured by the MMSE (with a score range of 15 to 30); global impression, rated by Participant’s Global Impression of Improvement (PGI-I) and Clinical Global Impression of Improvement (CGI-I); behavioral and psychological symptoms, monitored by Neuropsychiatric Inventory Questionnaire (NPI (25)); and caregivers’ burden, measured by Zarit’s Burden Interview (ZBI (26)). A specialized psychologist, who was blind to group assignment, scored all these outcomes except DEMQOL, DEMQOL-proxy, PGI-I, NPI and ZBI after a clinical interview. The psychologists conducted the assessments at baseline, Week 12, and the follow-up. The psychological evaluations at Week 12 and the follow-up had a 2 week window, respectively. Figure 2 summarizes the schedule for enrolment, intervention, and assessment. We will record any history of substance use disorder, dementia, psychiatric disorders, neurological disorders, brain injury and other conditions at baseline to exclude patients with clinically contraindicated conditions. Adverse events are any undesirable patient experience during PBM administration. We will monitor and record all adverse events throughout the study via self-report or clinical observations, regardless of causal relationship. We will follow up any untreatable adverse events after trial completion. The principal investigator will diagnose, treat, and explain any serious adverse events to the relevant patients. The subinvestigators will also report any information related to such adverse events to the principal investigator. The principal investigator is responsible for reporting any serious adverse events to the relevant authorities, including the clinical research review board, the Ministry of Health, Labour, and Welfare, and the pharmaceutical and medical device agencies.

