### Sequence generation

We will use a computer-generated stratified sequence from the Mujinwari system^2^ to assign participants to the active or sham PBM group in a 2:1 ratio. Our custom electronic data capture (EDC) system, based on Google Workspace For Business (Google, United States), will collect all data. A cloud computer will keep group assignment and other personal identification data. It will ensure a balanced distribution of diagnosis types (e.g., major neurocognitive disorder or mild neurocognitive disorder). This randomisation method stratifies by diagnosis, and the independent personnel can access the allocation results and provide the appropriate device. The principal investigator and subinvestigators can access each participant’s allocation and disclose it to the participants and raters only after the complete study data is consolidated.

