### Data research topic methods and data management

To evaluate the intervention, we will perform assessments by clinicians at baseline and Week 12 (Figure 2). Experienced psychologists unaware of the group allocations will conduct the baseline, Week 12 and follow-up evaluations. Participants and study partners will complete scheduled questionnaires and report adverse events between these visits. All data, except for the informed consent document, will be entered into the EDC anonymously and verified by independent data managers. Considering the device’s safety and the blindness of study personnel, we will not composite the specific data monitoring committee, but data monitors will oversee and review the trial progress. Participants can withdraw their consent or discontinue participating in the study at any time, but we will collect data as much as possible unless consent is withdrawn, or it is at least a serious deviation from the protocol. We will terminate the intervention if we observe any serious adverse events (SAEs). The following auditing standards for field work apply to this study based on the Clinical Research Act: audits will be conducted if any of the following criteria are met: (1) at least two SAEs that are causally related to the medical device are reported; (2) at least two serious protocol deviations are detected; (3) multicentre clinical trials are initiated; or (4) potential severe conflicts of interest that deviate from the prespecified plan for conflicts of interest are identified. We will report any necessary protocol amendments and their outcomes to both the clinical research review board and the Ministry of Health, Labour, and Welfare for registration on the Japan Registry of clinical trials website. After completing the trial, we will publish an original article to disseminate the data results.

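### The protocol conflicts with itself on whether participants withdrawn for insufficient efficacy or a serious violation still have the Week 12 ADAS-Cog and enter the primary analysis

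*Protocol article*

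**What the plan says.** **Intervention.** The list of criteria opens with "The participant will be withdrawn from the study if any of the following conditions apply", and the decision is taken "as determined by the principal investigator or subinvestigators". Two of the criteria matter here: "the device shows insufficient efficacy for the participant" and "there is a serious breach or violation of the research protocol". Insufficient efficacy has no threshold and no time point. Nothing in the section separates stopping the device from leaving follow-up.

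**Data management.** For participants who withdraw consent or discontinue, "we will collect data as much as possible unless consent is withdrawn, or it is at least a serious deviation from the protocol".

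**Outcomes.** "The main outcome of interest is mean change in ADAS-Cog scores from baseline to Week 12 between groups". On timing: "The psychologists conducted the assessments at baseline, Week 12, and the follow-up". No ADAS-Cog falls between baseline and Week 12.

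**Statistical analysis.** The primary analysis is described as intention-to-treat in all randomised patients. It is also said to use a Full Analysis Set that requires an observed efficacy assessment after the device is taken home. The only method named for missing data is imputation of the baseline score, as a sensitivity analysis. A per-protocol sensitivity analysis that excludes deviations is already planned.

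**The concern.** The three sections do not give one answer to a simple question: does a participant withdrawn under either criterion still have the Week 12 ADAS-Cog, and is that score analysed?

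The two criteria raise different problems.

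- **Insufficient efficacy.** The reason for leaving is linked to the outcome. If leaving the study means no Week 12 visit, the missing scores are missing because of poor response. An ANCOVA on observed scores does not correct that. Baseline imputation assigns no change to people who may have worsened.
- **Serious violation.** The Intervention and data management sections agree that follow-up may end. That contradicts the all-randomised analysis directly, whether these participants did well or badly.

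The planned sham arm has only 10 participants, so one or two selective losses there matter. A Week 12 score that was never collected cannot be restored by a later analysis plan.

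**Working it through.** **1. The sections side by side**

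| Reason for withdrawal | Intervention | Data management | Statistical analysis |
|---|---|---|---|
| Insufficient efficacy | Leaves the study | Collection continues after discontinuation; reach to investigator-led withdrawal unclear | All randomised patients, but an observed efficacy assessment is needed |
| Serious violation | Leaves the study | Collection may stop | All randomised patients; deviations excluded only per protocol |

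The first row is ambiguous. The second is a contradiction.

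**2. The plan's own figure**

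Inputs (Sample size calculation): difference 39.2 - 32.3 = 6.9, SD 4.8, two-sided alpha 0.05, power 0.80, two active per sham.

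Sham n = (1 + 1/2) x [4.8 x (1.960 + 0.842) / 6.9]^2 = 1.5 x 3.80 = 5.70, rounded up to 6. With 12 active the total is 18. Then 18 x 1.5 = 27, raised to 30. The figure reproduces. The margin for adherence and dropout is 3 of 30, or 10%.

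**3. Illustration of the bias if Week 12 scores are lost**

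Assumptions that are not in the document: normal change scores, SD of change 4.8, mean sham change 0, and no Week 12 score for anyone who worsens by more than t points. The true difference is the protocol's -6.9. Higher scores are worse.

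For an arm with mean mu, let c = (t - mu)/4.8. The share lost is 1 - Phi(c). The mean among those observed is m = mu - 4.8 x phi(c)/Phi(c). With baseline imputation the arm mean is Phi(c) x m.

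For t = 4:
- Sham: c = 0.833, 20.2% lost, m = -1.70.
- Active: c = 10.9/4.8 = 2.271, 1.2% lost, m = -7.05.
- Difference among those observed: -7.05 + 1.70 = -5.35.

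| t | Sham lost | Active lost | Observed scores only | Baseline imputed |
|---|---|---|---|---|
| 6 | 10.6% | 0.4% | -5.97 | -6.05 |
| 4 | 20.2% | 1.2% | -5.35 | -5.61 |
| 0 | 50.0% | 7.5% | -3.81 | -5.15 |

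If the true difference is 0, the same rule shifts both arms equally and the estimate stays at 0.

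**4. Power**

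Simulated trials of 20 versus 10, SD 4.8, with an assumed sham worsening of 1 point, half of those worsening by more than 4 points lost in both arms, and an unadjusted t-test:
- True effect -6.9: estimate about -6.1, power about 88%. Full-data power is about 95%.
- An assumed smaller effect of -5.6: estimate about -4.9, power about 72%. Full-data power is about 83%.
- No effect: type I error stays at about 5%.

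**5. Why these are upper bounds**

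The illustrations trigger withdrawal on the Week 12 score itself, which nobody has seen when the decision is made. An earlier judgement would rest on other information, such as the periodic remote reports. With the -5.6 effect and an assumed correlation of 0.5 or 0.3 between that information and the Week 12 change, the estimate is about -5.3 or -5.4 and power about 74 to 76%. Most of the remaining power loss then comes from having fewer participants.

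**The case against.** A reader might infer that the plan deletes the worst outcomes from the primary endpoint. It does not say so. The data management section keeps collecting data with two exceptions, withdrawn consent and serious deviation, and insufficient efficacy is neither. This stands, so loss of the score for that reason is a risk and not a rule. The limit of the defence is that the sentence speaks of participants who withdraw or discontinue, and does not clearly cover those whom the investigators remove.

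A reader might also infer a false benefit. If only active participants were lost, and there were no true effect, the scenario in step 4 would give about -0.9 points and a type I error of about 8.4%. But participants and assessors are blinded, and the investigators may access the allocation and "disclose it to the participants and raters only after the complete study data is consolidated". Nothing in the document supports withdrawal by arm, so this does not describe the trial as planned.

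A third tempting reading treats serious violators as poor responders. The document gives no such link.

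Finally, the article condenses a full protocol that is not shown, and procedures after discontinuation may be set out there. That is fair, but the sections that are shown conflict with one another, and this goes beyond an omitted detail.

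**Conclusion.** The concern holds as an inconsistency between the Intervention, data management and Statistical analysis sections. Severity: should-fix.

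For insufficient efficacy, the wording permits loss of the primary outcome for a reason tied to response. Under one blinded rule the likely direction is toward the null, with more sham than active participants lost, lower power and no inflation of type I error. The document gives neither the number of such withdrawals nor a threshold, so the size cannot be fixed. The figures of -6.0 to -3.8 for a true -6.9 rest on assumed thresholds, an assumed sham mean, the protocol's 4.8 used as the SD of change, and complete loss above each threshold. They are illustrative upper bounds.

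For serious deviations no simulation is needed. Ending data collection breaches the stated intention-to-treat analysis. It is not selective removal of poor scores.

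**What to change.** Reconcile the three sections by distinguishing two events: stopping the device, and ending follow-up.

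1. State that every randomised participant keeps the scheduled Week 12 and follow-up ADAS-Cog, whether or not the device is still used, unless consent is withdrawn or the participant cannot be reached or assessed.
2. State that this also covers withdrawals decided by the investigators.
3. Delete the serious-deviation exception to data collection, and handle deviations only in the per-protocol sensitivity analysis already planned.
4. Make the Statistical analysis section say plainly that these scores enter the primary analysis.

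The criteria for stopping the device stay with the investigators and are not judged here. The cost is a wording amendment and a few already scheduled visits kept for participants who stop the device. The sample size does not change.
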